### Recruitment

Prospective participants (intervention and control) will be recruited at the beginning of their pregnancy up to 28 weeks of gestation about interest and participation in the study. Participants will be recruited via advertisements on social media, fliers, and word of mouth. If an individual is interested in participating, they will contact the research team by completing the study screening questionnaire in REDCap or via telephone or email. Study personnel will contact the potential participant via telephone or email and explain the study in detail. Once interest is determined and screening eligibility is met, participants will be invited to sign a consent form and a medical release of information form and complete the baseline assessments at 20 to 28 weeks of pregnancy.

### Participant Allocation

Randomization allocation will be guided by the National Cancer Institute Clinical Trial Randomization Tool [32]. This tool generates an allocation scheme using the asymptotic maximal procedure. The following parameter inputs were used in the tool: trial size=60, maximum-tolerated imbalance=3; and arms (ratio 1:1). The output of this randomization allocation tool provides a schedule of randomization.

After signing the informed consent and release of medical record forms, participants will be emailed a secure link to complete the baseline enrollment surveys electronically in REDCap. In addition, each participant will be given the Healthy Pregnancy handout [33], Community Resources handout, and Birth Doula handout, in addition to the standard consent documents. Participants will be randomized according to the randomization schedule based on when they complete the enrollment surveys. Once a participant completes the enrollment surveys, the research coordinator will inform the participant of their group assignment and explain the procedures related to the assigned group.

Individuals randomized to the information control group will be dismissed and informed that they will be contacted by study personnel 6 to 12 weeks post partum to complete the follow-up assessments. Individuals randomized to the intervention group will be contacted by the doula interventionist to schedule their first doula session and be onboarded to the PARITY platform. The interventionist will explain that the participant will receive 3 additional sessions (4 in total) with the doula interventionist in addition to the mobile technology platform where communication can occur with the doula.

During the sessions, the doula interventionist will use the Doula Sessions Manual, which contains a script for each visit. The doula interventionist will track when contact is made with the participant on a form called the Intervention Fidelity Checklist. To ensure the fidelity of the intervention, the doula interventionist’s adherence to the intervention protocol will be measured through an audit of the dates and missed visits on the Intervention Fidelity Checklist and monthly review meetings.

All participants will complete postintervention surveys at 6 to 12 weeks post partum. At approximately 12 weeks post partum (or upon the receipt of records), participant medical records will be accessed to extract the pertinent outcome data. A total of 10 to 15 participants in the intervention group will be approached about completing the qualitative portion of the study. Participants will be approached in order based on the study’s completion date.

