### Study Population

Participants will be included in the study based on the following criteria: (1) self-identify as being of Black race, (2) pregnant with gestational age 20 to 28 weeks at enrollment, (3) ability to read and write in the English language, (4) planning to give birth in a health care facility and receive obstetrical care with a health care record, (5) reside within 20 minutes of the identified metropolitan area, (6) 19 to 51 years of age, and (7) own a smartphone with internet access. Participants will be excluded from the study for the following reasons: (1) current involvement in another intervention study, (2) planned pregnancy termination, or (3) inability to provide informed consent.

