### Intervention

#### Overview

The PARITY program is designed to occur throughout the pregnancy continuum (first trimester through 12 months post partum). For the purposes of this study, the PARITY program will be shortened in length and scope to show feasibility for a larger trial. Participants will be enrolled in the study from 20 to 28 weeks’ gestation of pregnancy and will complete postintervention surveys at 6 to 12 weeks post partum. All participants (intervention and information control groups) will receive routine care from obstetric providers (not paid for by the study), printed materials about having a healthy pregnancy, printed materials about community resources, and printed materials with a referral to a birth doula if interested (paid for by the study as an incentive).

The PARITY program involves 2 parts. The first is a wellness technology platform that includes a wellness curriculum and reinforcing SMS motivational messages with links to in-depth wellness content. The second is Black community–based doula support, delivered both in-person and through the technology platform.

The mobile technology component of the intervention is a web-based platform hosted by GoMo Health delivered over a 12-week period and will end before birth [28]. The platform includes web pages with various pregnancy-related wellness content. The content is evidence based, tested by GoMo Health, and based on our preliminary research [21,28]. Participants will receive SMS *text* messages from the web platform, and at times these will include hyperlinks. The doula will be able to communicate with participants, reinforce its content, and hold the intervention sessions within this platform [28]. The platform was approved by the University of Nebraska Medical Center Information Technology Services and is compliant with the Health Insurance Portability and Accountability Act. Participants in the intervention group will receive 4 sessions with the doula interventionist within the technology platform and 12 weeks of tailored wellness, strengths, and health care adherence curriculum and SMS text messaging through the platform. There is a comprehensive database to track calls, opened hyperlinks, and participant engagement with the platform.

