#### Doula Sessions

Each participant will work with a Black community–based doula interventionist who will communicate with them via the PARITY mobile technology platform during the study. The doula interventionist will have certifications as a doula and training in emotional and educational support, pregnancy health, privacy and confidentiality, inspiring change (theories of health), various learning styles, health literacy, and cultural competency. All doula sessions will be conducted by the same doula interventionist, who will be blinded to all outcome data.

The SMS text messaging will be sent in the doula’s voice. The doula interventionist will communicate with each participant in 4 live sessions lasting 30 to 60 minutes. These live conversations will include basic instruction and open-ended conversations focused on reinforcing strengths and wellness habits. In addition, these check-ins will promote health care adherence and provide guidance on navigating the health care system. The doula interventionists will assist participants through the strengths-focused framework of maternal adaptive capacity to identify and understand each participant’s particular barriers to wellness and health care adherence and to design approaches that increase behavioral change [24]. The doula interventionist will suggest community resources based on the participant’s needs.

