### Outcome Measures

At enrollment, participants will sign a medical release of information form allowing the research team to measure data retrospectively from the participant’s medical records. To collect the self-report questionnaires for the enrollment and postpartum assessments, each participant will use a unique, secure link to complete the electronic questionnaires in REDCap at baseline after informed consent is signed and at 6 to 12 weeks post partum based on the participant’s due date. Reminders from the research team will be sent to participants using various forms of contact (phone and email) to complete the questionnaires as needed.

The following outcome measures will be used to examine the feasibility and acceptability of the PARITY intervention:

Feasibility will be assessed through enrollment, attrition, adherence to the intervention, and data collection.Enrollment rate: enrollment will be measured by the percentage of eligible individuals who agree to participate in the trial.Attrition rate: attrition will be measured by the percentage of eligible individuals who complete the study.Adherence to the intervention: adherence to the intervention will be measured using the Intervention Fidelity Checklist, where the doula interventionist will track when contact is made with participants and the number of doula sessions completed. Engagement with the platform will be tracked through clicks and the time spent on the platform.Data collection: data collection feasibility will be measured through study personnel’s sense of ease of use, time required, and missing data.Acceptability of and experiences with the intervention will be assessed using in-depth qualitative information gathered through interviews with intervention participants at 6 to 12 weeks post partum. Interviews will solicit (1) the usefulness of the intervention, (2) ideas to improve the intervention, (3) satisfaction with the intervention, and (4) the utility of innovative technology to deliver the intervention. The qualitative interviews will be audio recorded and transcribed verbatim.

The following outcome measures will be used to examine the preliminary efficacy of the PARITY intervention:

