### Sample Size Calculation for Future Full-Scale RCT

A sample size of 25 participants per group is sufficient to measure the proportional outcomes of recruitment efficiency and attrition for each group separately with an SE ≤0.10, assuming no attrition and worst-case variability (0.25) in each group. Past research suggests that attrition of up to 20% is acceptable and limits bias [26,27]. If there is up to 20% attrition in each group, the SE for each proportional outcome will be ≤0.12.

On the basis of Welch 2-sample 2-tailed *t* test, a minimum sample size of 25 participants per group provides 80% power to measure a difference in mean blood pressure and gestational weight change between the intervention and control groups of 0.81 multiplied by the SD, using a significance level of .05 [25]. If there is up to 20% attrition in each group, a difference of 0.91 multiplied by the SD is detectable with 80% power using a significance level of.05 [25]. We will recruit at least 5 additional participants per group, planning for screen failures or participant withdrawals.

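### Controls have no stated study contact between assignment and the postpartum survey, while PARITY participants do, which creates a risk of unequal survey non-response

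*Protocol article*

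**What the plan says.** All places are in the protocol article.

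- **Control arm.** Under Participant Allocation: "Individuals randomized to the information control group will be dismissed and informed that they will be contacted by study personnel 6 to 12 weeks" after birth. No contact in between is described.
- **PARITY arm.** Under Doula Sessions: "The doula interventionist will communicate with each participant in 4 live sessions lasting 30 to 60 minutes". The platform component is "delivered over a 12-week period and will end before birth" (Intervention, Overview), and the Strengths section counts 24 text messages over those 12 weeks.
- **Follow-up survey.** Under Participant Allocation: "All participants will complete postintervention surveys at 6 to 12 weeks post partum". According to Outcomes, the questionnaires on wellness behavior and empowered strengths are taken at baseline and at this one later point only.
- **Clinical outcomes.** At about 12 weeks post partum, "participant medical records will be accessed to extract the pertinent outcome data". The release for this is signed at enrollment.
- **Safeguards for both arms.** "Reminders from the research team will be sent to participants using various forms of contact (phone and email) to complete the questionnaires as needed" (Outcome Measures). Ethical Considerations adds a US $50 gift card for completing follow-up. Data Analysis accepts that dropout may depend on unobserved outcomes and plans a pattern-mixture reanalysis.
- **Attrition allowance.** The sample size section works with the condition "If there is up to 20% attrition in each group".

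**The concern.** Three intake and behavior questionnaires (nutrition, physical activity, sleep) and six strengths scales make nine measures that rest on one post-baseline web survey. Someone who misses it has no follow-up value on any of them. One arm stays in regular touch with a study doula for much of the pregnancy, while the other is released and asked months later to respond. Phone numbers change and interest fades over such a gap. The survey is also timed from the due date, and the article describes no step for learning the actual delivery date.

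Two things are at stake. The between-arm comparison on these nine measures could be distorted if more controls fail to respond and the non-responders differ from the responders. And retention, which the Objectives name as key information from this pilot, would for controls partly measure the contact schedule.

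**Working it through.** **1. The plan's own figures.** For a two-sample two-sided t test at .05 with 80% power, the noncentral t distribution gives a detectable difference of 0.809 SD with 25 per arm and 0.909 SD with 20 per arm (25 less 20%). These reproduce the stated 0.81 and 0.91. The standard error of a proportion, sqrt(0.25/n), is 0.100 at n = 25 and 0.112 at n = 20, in line with the stated limits of 0.10 and 0.12. The sample size arithmetic is sound and serves here only as a yardstick.

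**2. Interval without contact.** Inputs from the document: entry when "pregnant with gestational age 20 to 28 weeks at enrollment", survey at 6 to 12 weeks post partum, programme of 12 weeks. Assumptions: birth at 40 weeks, programme start at enrollment, full 12 weeks delivered.

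Control interval = (40 − weeks at enrollment) + survey week. PARITY interval = the same − 12.

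| Enrolled at | Survey week | Control | PARITY |
|---|---|---|---|
| 20 | 6 | 26 | 14 |
| 20 | 12 | 32 | 20 |
| 28 | 6 | 18 | 6 |
| 28 | 12 | 24 | 12 |

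The ranges are 18 to 32 weeks for controls and 6 to 20 weeks for PARITY. The 12-week gap between arms depends on the assumptions. For example, with enrollment at 28 weeks, birth at 38 weeks and the survey at week 6, a control waits 38 − 28 + 6 = 16 weeks. A PARITY participant has at most 10 weeks of programme and then waits 6, so the gap is 10 weeks.

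**3. Possible bias.** Let a be the share lost in an arm, and k the responder mean minus the non-responder mean, in SD, taken as equal in both arms. The responder mean exceeds the full-arm mean by a × k, so

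bias in (PARITY − control) = k × (a_PARITY − a_control).

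The document gives no attrition rate by arm and no k, so the following values are assumptions. With 30 per arm:

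| Attrition PARITY / control | Responders | Size of bias, k = 0.3 | Size of bias, k = 0.5 |
|---|---|---|---|
| 20% / 20% | 24 / 24 | 0 | 0 |
| 10% / 30% | 27 / 21 | 0.20 × 0.3 = 0.06 SD | 0.20 × 0.5 = 0.10 SD |
| 10% / 40% | 27 / 18 | 0.30 × 0.3 = 0.09 SD | 0.30 × 0.5 = 0.15 SD |

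On a scale where higher is better, if responders do better (k > 0) and more controls are lost, the bias is negative and pulls a true benefit toward zero. If responders do worse, it inflates the benefit. If k = 0 or the losses are equal, there is none.

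**4. Precision and detection.** At 27 and 21 responders the standard error of the difference is sqrt(1/27 + 1/21) = 0.29 SD, so 0.06 to 0.10 SD is about 0.2 to 0.3 of one standard error. The detectable difference is 0.833 SD, against 0.826 SD at 24 and 24, so little power is lost. With 30 per arm, the power to detect 90% against 70% completion is only about 49%, so a real imbalance could go unnoticed if it were judged by a test.

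**The case against.** Much of the other side stands. The document gives no attrition rate by arm. Bias needs loss that is both unequal and related to outcome beyond what the model conditions on. Contact is the intervention, so an information-only control will always have less of it, and retention under that control is a fair thing for a pilot to measure if the larger trial keeps the same schedule. Both arms receive the same follow-up payment and the same reminders, and both are offered a study-paid birth doula. The PARITY arm has its own silent interval after the programme ends. The sample size section already intends to measure attrition in each group separately. Routine tracing could also sit in the standard operating procedures.

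Four stronger readings are tempting, and the document supports none of them.

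- **Unequal attrition is built in and the survey results are biased.** Only the unequal contact is stated. Unequal loss and its link to outcome are possibilities.
- **The attrition allowance assumes equal loss and is therefore contradicted.** It sets a ceiling of 20% per group, which unequal losses can satisfy. The differences of 0.81 and 0.91 SD concern blood pressure and weight change, which come from charts.
- **The controls' gap is always 12 weeks longer.** That holds only under the timing assumptions above, and Challenges and Limitations expects varying intervention doses because birth timing is inexact.
- **The primary outcome is at risk.** Blood pressure, weight gain, cesarean birth and appointment adherence come from the medical record.

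The safeguards do not dispose of the point. Payment and questionnaire reminders work only if the participant can still be reached. With one follow-up survey, a non-responder adds no post-baseline survey data, so a pattern-mixture model must rest on assumptions the data cannot test. With perhaps 3 to 9 non-responders per arm it cannot be relied on to repair the comparison.

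**Conclusion.** The point holds as a risk in a stated contact schedule, not as a demonstrated bias. Under birth at 40 weeks and programme start at enrollment, controls go about 18 to 32 weeks and PARITY participants about 6 to 20 weeks without contact before the survey. The exposure is limited to the nine questionnaire outcomes of objective 3 and to the control retention estimate. In the main assumed scenario the bias is 0.06 to 0.10 SD, in either direction, well below both the standard error of about 0.29 SD and the detectable difference of 0.81 to 0.91 SD. It would not decide the trial. It is worth acting on because prevention is cheap, later statistical correction would be weak, and by-arm retention is something the pilot is meant to deliver.

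**What to change.** Under Participant Allocation, replace the dismissal of controls with one keep-in-touch schedule that is identical in both arms and carries no health content. For example, send an automated message at about 36 weeks and another around the due date, asking only for confirmation of contact details and the delivery date. The second message also lets the survey be timed from the actual birth.

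Report survey completion by arm with all randomized participants as the denominator. Outcome Measures currently counts completers among eligible individuals, which is a different quantity. Describe any difference with its interval, since a non-significant test would mean little at this size.

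The cost is a small amendment and two automated messages per participant. The downside is slight extra contact for controls, kept neutral and the same in both arms. The article describes enrollment as ongoing, so if the change comes mid-trial, record its date and report retention before and after it.

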### Ethical Considerations

This protocol was approved by the University of Nebraska Medical Center Institutional Review Board (IRB; #0076-23-EP). Participants must sign an informed consent form before participating in the study. The consent process involves a detailed description of the study, describing any participation risks, indicating that participation is voluntary and that the participant has the right to withdraw at any time. Informed consent will be obtained in a private, quiet location to facilitate discussion and thoughtful consideration. Research team members will assess participants’ capacity to consent, answer questions, and ensure understanding.

To maintain participant confidentiality, all study data will be deidentified. Each participant will be assigned an identification code for use on all study materials. The link between a participant’s name and identification code will be stored only on the consent form, which will be kept in a locked file in the principal investigator’s office, separate from other study materials. Data sources include consent forms; medical records; transcribed interviews, handwritten notes; and data entered in REDCap, a secure web-based application for research data management [30,31]. Hard copies of any data will be stored in a locked file accessible only to the investigators or the IRB. All electronic data, including entries in REDCap, will be password protected and encrypted. Medical record data will be encrypted and transmitted through secure firewalls. All transcripts from the qualitative interviews will be deidentified, encrypted, stored in a locked facility, and available for analysis and review only by study staff. Only study personnel, the research sponsor, the IRB, and legally authorized individuals will have access to the research records. Upon study completion, all personal health information will be removed from the database. Study findings will be published in scientific journals or presented at meetings without revealing patient identities.

Participants will receive a US $50 gift card for completing baseline assessments and US $50 for completing follow-up assessments. Participants in the qualitative portion of the study will be compensated with a gift card valued at US $25.

### Outcome Measures

At enrollment, participants will sign a medical release of information form allowing the research team to measure data retrospectively from the participant’s medical records. To collect the self-report questionnaires for the enrollment and postpartum assessments, each participant will use a unique, secure link to complete the electronic questionnaires in REDCap at baseline after informed consent is signed and at 6 to 12 weeks post partum based on the participant’s due date. Reminders from the research team will be sent to participants using various forms of contact (phone and email) to complete the questionnaires as needed.

The following outcome measures will be used to examine the feasibility and acceptability of the PARITY intervention:

Feasibility will be assessed through enrollment, attrition, adherence to the intervention, and data collection.Enrollment rate: enrollment will be measured by the percentage of eligible individuals who agree to participate in the trial.Attrition rate: attrition will be measured by the percentage of eligible individuals who complete the study.Adherence to the intervention: adherence to the intervention will be measured using the Intervention Fidelity Checklist, where the doula interventionist will track when contact is made with participants and the number of doula sessions completed. Engagement with the platform will be tracked through clicks and the time spent on the platform.Data collection: data collection feasibility will be measured through study personnel’s sense of ease of use, time required, and missing data.Acceptability of and experiences with the intervention will be assessed using in-depth qualitative information gathered through interviews with intervention participants at 6 to 12 weeks post partum. Interviews will solicit (1) the usefulness of the intervention, (2) ideas to improve the intervention, (3) satisfaction with the intervention, and (4) the utility of innovative technology to deliver the intervention. The qualitative interviews will be audio recorded and transcribed verbatim.

The following outcome measures will be used to examine the preliminary efficacy of the PARITY intervention:

Maternal blood pressure (primary) at 20 weeks, 36 weeks, birth, and 6 weeks post partum will be measured retrospectively from the medical record at 12 weeks post partum. The data will be analyzed as a continuous variable using the participant’s blood pressure (systolic and diastolic) as well as categorically with the blood pressure classifications of hypertension (>140/90) and severe hypertension (>160/110).Gestational weight gain (secondary), or the amount of weight gained in pounds at 20 weeks, birth, and 6 weeks post partum, will be measured retrospectively from the medical record at 12 weeks post partum.Cesarean birth (secondary) will be assessed from the delivery modality (vaginal, cesarean, or assisted vaginal delivery), measured retrospectively from the medical record at 12 weeks post partum.Perinatal outcomes (exploratory) from birth will be measured retrospectively at 12 weeks post partum via the maternal medical record. The perinatal outcomes that will be measured include preterm delivery; gestational diabetes; birth weight; gestational age at delivery; anesthesia used during labor; labor length; delivery provider type (obstetric physician, family physician, resident physician, or certified nurse midwife); and intrapartum medical diagnoses according to theInternational Classification of Diseases, 10th Revision[34], including hypertensive disorders of pregnancy, intrapartum fever, and postpartum hemorrhage. In addition, the Appearance, Pulse, Grimace response, Activity, and Respiration score of the newborn at birth will be measured as a way to summarize the health of the baby [35].

The following outcome measures will be used to investigate changes to wellness behavioral outcomes and empowered strengths:

Wellness-related behavioral outcomes:*Nutritional intake* will be measured with the Multifactor Screener, 2000, as used in the Observing Protein and Energy Nutrition Study [36]. This instrument measures approximate intakes of fruits and vegetables and percentage energy from fat and fiber. Respondents will report through a self-administered questionnaire in REDCap how frequently they consume foods in 16 categories and the type of milk consumed. The questionnaire will measure nutrition at baseline and 6 to 12 weeks post partum.*Physical activity* will be measured with the International Physical Activity Questionnaire-Short Form (IPAQ-SF) [37]. The IPAQ-SF consists of 9 items and collects information on the time spent walking, in vigorous and moderate intensity activity, and in sedentary activity over the last 7 days. It is scored by converting the reported time into metabolic equivalent of task (MET) minutes. The MET minutes are then summed to provide an understanding of an individual’s physical activity levels, with low levels being <600 MET minutes per week, moderate activity levels being 600 to 2999 MET minutes per week, and high activity levels being ≥3000 MET minutes per week [37]. It will be self-administered in REDCap and takes approximately 10 minutes to complete. The IPAQ-SF is a reliable (α>.80) and valid instrument [37]. Physical activity will be measured at baseline and 6 to 12 weeks post partum.*Sleep quality* will be measured using the Pittsburgh Sleep Quality Index, a reliable (α>.83) and valid self-report questionnaire that assesses sleep quality over a 1-month time interval [38]. The measure consists of 19 individual items, creating 7 component scores that range from 0 to 3 points. The 7 component scores are summed to produce 1 global score that ranges from 0 to 21 points, with 0 indicating no difficulty and 21 indicating severe difficulty across all areas [38]. Sleep quality will be measured through a self-administered survey, which takes about 15 minutes to complete, in REDCap at baseline and 6 to 12 weeks post partum.*Health care adherence* will be measured by the number of health care appointments attended and missed, which will be logged in the medical record. Health care adherence will be measured throughout the pregnancy continuum and collected at 12 weeks post partum retrospectively via the medical record.Empowered strengths:*Self-efficacy* will be measured using the General Self-Efficacy scale [39] administered in REDCap. The General Self-Efficacy scale is a valid and reliable (α>.75-.90) 1D self-report measure that features a 10-item questionnaire assessing the optimistic self-beliefs of individuals to cope with various challenging demands in life [39]. It takes approximately 5 minutes to complete. The response options are presented along a Likert scale for each item, ranging from 1 (not at all true) to 4 (exactly true). The total score is calculated as the sum of the items, with a higher total score indicating more self-efficacy [39]. Self-efficacy will be measured at baseline and 6 to 12 weeks post partum.*Social support* will be measured using the 10-item Social Provisions Scale [40]. The 10-item Social Provisions Scale is a validated and reliable (α>.80) measure that assesses 5 social provisions: attachment, guidance, social integration, reliable alliance, and reassurance of worth [40]. Each item is rated on a 4-point Likert scale, ranging from 1 (strongly disagree) to 4 (strongly agree), and the individual item scores are then summed to provide a summary score ranging from 10 to 40 [40]. Higher scores indicate higher levels of social support [41]. Social Support will be measured through a self-administered survey, which takes approximately 5 to 10 minutes to complete, in REDCap at baseline and 6 to 12 weeks post partum.*Motivation* will be measured with the Self-Motivation Inventory (SMI) [42]. The SMI is a 40-item, 5-point Likert scale questionnaire that will be self-administered in REDCap and takes about 15 minutes to complete. The SMI is a valid and reliable (α>.91) instrument measuring self-motivation conceptualized as perseverance independent of external support [42]. Motivation will be measured at baseline and 6 to 12 weeks post partum.*Resilience* will be measured using the 10-item Connor-Davidson Resilience Scale [43]. The 10-item Connor-Davidson Resilience Scale is a valid and reliable (α>.85) unidimensional self-reported scale measuring resilience [43]. Respondents will self-report through a survey in REDCap by rating items on a 5-point Likert scale ranging from 0 (not true at all) to 4 (nearly all of the time). Scores range from 0 to 40, with higher scores representing higher resilience [43]. Resilience will be measured at baseline and 6 to 12 weeks post partum through the survey, which takes about 5 minutes to complete.*Problem-solving* will be measured with the Problem-Solving Inventory (PSI) [44]. The PSI is a valid and reliable (α>.86) self-report instrument that measures how well individuals make decisions and their problem-solving abilities [44]. The PSI includes 32 items using a 6-point Likert scale and takes about 10 minutes to complete. The total score of the questionnaire is the sum of all responses, with lower scores representing lower problem-solving abilities [44]. Problem-solving will be measured through a self-administered survey in REDCap at baseline and 6 to 12 weeks post partum.*Self-regulation* will be measured with the Index of Self-Regulation (ISR) [45]. The ISR is a valid and reliable (α>.87) instrument that measures the level of self-regulation for health behavior change in a 9-item scale [45]. Respondents rate items on a 5-point Likert scale, ranging from 1 (strongly disagree) to 6 (strongly agree), with higher sum scores indicating higher levels of self-regulation for a behavior [46]. Self-regulation will be measured at baseline and 6 to 23 weeks post partum in REDCap through the ISR, which takes about 5 to 10 minutes to complete [46].Other variables that will be assessed are demographics, discrimination, and neighborhood:*Demographics:* an investigator-developed form will measure demographic variables, including income, education, ethnicity, insurance, health provider, relationship status, and pregnancy history, at baseline.*Discrimination:* discrimination will be measured using the Everyday Discrimination Scale [47] through a self-administered survey in REDCap. The Everyday Discrimination Scale is a valid and reliable (α>.74) instrument that measures the frequency of chronic and routine unfair treatment in everyday life [47]. Respondents are asked to report how often they experience unfair treatment in their day-to-day life on a 6-point Likert scale ranging from 1 (never) to 6 (almost every day), with total scores ranging from 10 to 60. Higher scores indicate experiencing discrimination frequently and in a variety of situations [47]. Discrimination will be measured at baseline.*Neighborhood:* neighborhood variables will be assessed using the Neighborhood Collective Efficacy-Community Cohesion and Informal Social Control protocol from the Project on Human Development in Chicago Neighborhoods [48]. This valid and reliable (α=.82) measure includes 10 Likert-style questions that assess trust and expectations among neighbors and is used to determine how the neighborhood environment modifies risky behaviors [48]. It will be self-administered as a survey in REDCap and takes about 10 minutes to complete. The measures consist of 2 subscales, Community Cohesion and Informal Social Control, that include 5 Likert-style items, each ranging from 1 (strongly disagree) to 5 (strongly agree). Higher scores indicate greater neighborhood collective efficacy [48]. Neighborhood variables will be measured at baseline.
